### Participant timeline {13}

The participant timeline is shown in Table 1.

**Table 1 Tab1:** Mobile Men study schedule of enrolment, interventions, and assessments

	**Enrolment**	**Allocation**	**Randomisation phase**						**Choice phase**		**Close-out**
**Timepoint**	**0**	**0**	**M0**	**M1**	**M3**	**M4**	**M5**	**M7**	**M9**	**M10–17**^**1**^	**M18**
**Enrolment**											
Eligibility screen	X										
Informed consent	X										
Allocation		X									
**Intervention**											
CAB-LA injection			X	X	X		X	X			
Oral PrEP dispensed			X	X		X		X			
**Assessments**^**2**^											
Locator information	X			X		X			X	X	
Demographics	X										
Risk and mobility (short CRF)	X			X	X	X	X	X	X	X	
Risk and mobility (Long CRF)	X								X		X
PrEP adherence				X	X	X	X	X	X	X	X
Adverse events			X	X	X	X	X	X	X	X	X
IDIs				X		X	X		X	X	X
FGDs				X					X		X
Surveys	X								X		X
HIV test	X			X	X	X	X	X	X	X	X
STI screen	X								X		
DBS	X			X	X	X	X	X	X	X	X
Blood pressure	X				X	X			X	X	X
BMI	X				X	X			X	X	X
CrCl if ≥ 30 years	X										
HepBsAg	X										

^1^Visit schedule for choice phase is dependent on choice of PrEP made at month 9 and at each subsequent visit. ^2^Done at visits corresponding to the intervention received by the participant; *CAB-LA*, long-acting injectable cabotegravir; *PrEP*, preexposoure prophylaxis; *CRF*, case report form; *IDIs*, Iin-depth interviews; *FGDs*, focus-group discussions; *HIV*, human immunodeficiency virus; *STI*, sexually transmitted infection; *DBS*, dried blood spot; *BMI*, body mass index; *CrCl*, creatinine clearance; *HepBsAg*, hepatitis B surface antigen

### Sample size {14}

The planned enrolment sample size of 400 participants (randomised) will allow 80% power to detect an absolute difference of 11% in persistence between trial arms at a 5% significance level, assuming 80% persistence in the lower persistence arm [40] (and 91% persistence in the higher persistence arm) and allowing for 20% lack of ascertainment of persistence, for example, due to medical ineligibility to receive the randomised intervention or death. If the persistence in the lower persistence arm is lower, at 60% [41], then we will have 80% power to detect an absolute difference of 15% (i.e. 60% versus 75% persistence). Sample size is calculated using standard methods for comparing two proportions and implemented using the “power two proportions” command in STATA.

### Recruitment {15}

#### Preparatory work

Preliminary work in the communities is being carried out, including a rapid ethnographic assessment study to inform and facilitate study implementation. Demand creation for PrEP will be achieved through a community engagement campaign and peer and sex worker outreach activities prior to and during the study start. These efforts will expose men in the communities to PrEP educational materials and encourage them to visit community and public health sites to access sexual health services, including PrEP. Potential participants will be provided with educational information about each of the PrEP products both during the enrollment visit and as part of the broader community-wide demand creation campaign preceding the study.

### Masaka, Uganda

Recruitment efforts will mainly focus on landing sites around the shores of Lake Victoria in Masaka District. These fishing communities have a high HIV burden that is attributed to several factors, including high mobility, sex work, relatively young populations with disposable daily income, and inadequate health services. People in these communities frequently move between different landing sites and islands, with up to 47% of men and 25% of women reporting being away from home for at least 2 days each month. This mobility is mainly driven by the seasonal fish catch. Previous studies have highlighted that such high mobility can limit access to health services, increase HIV infection risk, and underscore the need for tailored HIV prevention interventions that account for these mobility patterns [39, 42]. The Mobile Men study has been designed to address these challenges.

The study team will work with local leaders and members of Village Health Teams and via community HIV testing services to identify potential participants from places of entertainment (such as lodges/guest houses, bars) and from their homes. Detailed locator information, including addresses, telephone contacts, and next-of-kin details, will be collected to facilitate effective phone and/or physical tracing during the follow-up phase of the study.

### Buffalo City Metro (BCM) Municipality, Eastern Cape, South Africa

The Eastern Cape province is a historically under-resourced and under-researched province. Since 1990, Eastern Cape has ranked last among South Africa’s nine provinces in its Human Development Index score [43, 44]. In 2022, the estimated HIV prevalence in the province was 19.4% among individuals aged 15 to 49 years. That same year, an estimated 92.6% of individuals living with HIV in Eastern Cape knew their status, 74.9% were on ART, but only 62.6% were virally suppressed (Viral load < 1000 copies/mL) [45, 46]. Given that South African men are less likely to know their HIV status, initiate ART, or be virally suppressed compared to women, we expect these indicators will be worse for men in the province [47].

Within BCM, men will be recruited from Duncan Village (urban) and Mdantsane (peri-urban) townships. These predominantly black, Xhosa-speaking communities have some of the highest HIV prevalence rates in South Africa. Both Duncan Village and Mdantsane are densely populated, with many residents living in informal housing. Mdantsane, in particular, is one of the largest townships in the country. Mobile men from these communities return home on a regular basis to visit their extended families. Recruitment will target men who sit by the roadside waiting for offers of casual labour. Previous studies have reported an HIV prevalence of 16.6% in this population [48]. Additionally, construction workers and migrant workers (men who leave their partners and families to work) will be recruited. Truck drivers will also be targeted through nurse-led primary healthcare services at a fixed roadside Wellness Centre located near East London’s shipping port and airport. The centre serves an extremely busy route for the long-distance goods transport.

### KwaZulu-Natal, South Africa

Recruitment will focus on mobile young men from a busy urban and peri-urban taxi rank and market area in Mtubatuba town in uMkhanyakude where the main N2 highway intersects with the R618 route to St. Lucia and surrounding areas. This primarily rural area faces significant economic challenges compared to other regions in South Africa, with high levels of unemployment. For example, over 85% of young people aged 20–24 are unemployed. The uMkhanyakude district also has a very high HIV prevalence of 30% [49]. Healthcare infrastructure is limited, with only 1 public hospital and 13 fixed-location primary healthcare clinics, all of which face resource constraints in delivering HIV prevention and health promotion [50]. Men looking for work, or on their way to find work in the larger urban setting of Durban and Johannesburg, the Richards Bay shipping port, the coalmines, and sugar plantations of uMkhanyakude, will mostly transition through the taxi rank and market area of Mtubatuba. It is also a hub where men who move for work spend their earnings on food, sex work/transactional sex, other recreational activities, and alcohol. Stakeholder engagement, key informant interviews, and rapid ethnographic assessments prior to the study suggested that mobile clinics based in Mtubatuba taxi rank that provide hypertension and diabetes screening, and are supported by peer and sex worker outreach, would reach men who are mobile for work.

## Assignment of interventions: allocation

### Sequence generation {16a}

The allocation sequence will be generated using computer-generated random numbers using STATA. Randomisation will be done in a 1:1 ratio, stratified by setting (three groups) and using randomly permuted block size.

### Concealment mechanism {16b}

The generated allocation sequence will then be embedded within the data collection system (REDCap). At the time of enrolment, each participant will be given a unique randomisation identifier in the temporal order in which they are randomised within their setting. The trial arm allocation for this unique identifier will then be accessed in REDCap. The trial arm allocation will be hidden until the participant has received their unique randomisation identifier.

### Implementation {16c}

The allocation sequence will be written by the trial statistician and with the random seed chosen by a statistician who is otherwise uninvolved with the study. Participants will be enrolled by clinicians. After determining a participant’s eligibility, the clinician will log onto REDCap using their personal access credentials. REDCap will then prompt the clinician to confirm eligibility of the site, and that they want to randomise a new participant with the next randomisation ID for that site to the trial. Once confirmed, the participant is randomised by the clinician and assigned to a randomisation arm according to the next unique identifier on the allocation list. The randomisation allocation assigned will now be read-only and cannot be edited after this.

## Assignment of interventions: blinding

### Who will be blinded {17a}

Due to the nature of the trial, it is not possible to blind participants, study staff involved with participant care, or outcome assessors. Furthermore, data analysis will also be done unblinded due to the different schedules followed by participants depending on the trial arm to which they are allocated, which relates directly to how outcomes are ascertained and prohibits a blinded analysis.

### Procedure for unblinding if needed {17b}

Not applicable. This is an open-label study.

## Data collection and management

### Plans for assessment and collection of outcomes {18a}

#### Collection of clinical, sociodemographic, and behavioural data

Participants’ weight, height, and blood pressure will be measured at screening and at specified follow-up visits (Table 1), as injectable PrEP is potentially associated with weight gain and hypertension.

Sociodemographic, behavioural, risk, and mobility information will be collected through surveys at baseline and specified follow-up visits (Table 1). PrEP-related data, including details of the PrEP provided to and used by the participant, will be documented at each visit. During the “choice period” (9 to 18 months), participants will be asked at each visit to indicate their preferred PrEP intervention. For participants who choose to switch PrEP options, their reasons will be captured on a PrEP switch CRF. To evaluate PrEP adherence and ensure consistent counselling, a PrEP adherence CRF will be administered by a study team member at every visit. The PrEP adherence questionnaire will focus on the following:Self-reported PrEP use, including whether participants are currently taking PrEP, the number of days since their last PrEP tablet, and adherence surrounding condomless sex (e.g. the number of tablets taken the day before and after the sexual act)Any adverse clinical or social effects experienced as a result of PrEP useReasons for pausing or discontinuing PrEP

### Collection of laboratory data

The following laboratory tests will be performed at screening and specified time points (Table 1) to confirm participant eligibility and the safety of product use.HIV testing: HIV will be confirmed at each in-person visit using the national HIV testing algorithm. Participants who test positive during the trial will be counselled and referred to local clinical centres for HIV care and treatment.Hepatitis B viral (HBV) testing: A blood sample will be collected at screening to test for hepatitis B infection using the site’s routine test for hepatitis B surface antigen.Creatinine clearance: Serum creatinine levels will be measured at screening for men aged 30 years and older. Subsequent testing will be conducted if clinically indicated.DBS: These samples will be collected and stored for later retrospective analysis of drug levels of drug levels and possibly viral load testing.Sexually transmitted infections (STIs): Testing for STIs, including gonorrhoea, chlamydia, and syphilis, will be performed based on local guidelines.

### Collection of social and economic science implementation data

To answer the secondary implementation objectives of reach, adoption, implementation, and maintenance using the RE-AIM implementation science framework (Table 2), a mixed-methods data collection approach will be adopted.

**Table 2 Tab2:** The proposed RE-AIM evaluation

Domain definition	Implementation outcome	Data source
*R*each	*Client (user) level*: The extent to which mobile men at risk of HIV acquisition effectively take up PrEP measured as the patterns of uptake and persistence per arms and community experience	Rapid ethnographic assessments of each community and the surveys and process of engagement with services
*E*ffectiveness	*Client (user) level*: Increased effective use (adopt and adhere) of PrEP amongst mobile men. Measured as proportion of participants who are retained on PrEP and participant choice	Pragmatic randomised controlled trial (RCT)
*A*doption	*Client (user) level*: Acceptability (uptake when offered), attitudes towards, preferences/choices, and patterns of use amongst different groups of mobile men	Pragmatic RCT, surveys, qualitative interviews with service users & process of engagement with services, and exit interviews
*I*mplementation	*Provider (service) level*: Appropriateness, feasibility, practicability, and fidelity of CAB-LA in the three stages or initiation, continuation, and safe stopping with national HIV testing algorithms	Qualitative data from service providers, time motion studies, and HIV self-testing study
*M*aintenance	*Provider and health systems level*: Affordability and resources needed for scalability	Time motion studies and costing and modelling

Data collection methods will include the following:

#### Rapid ethnographic assessments

These assessments will be conducted at baseline, after 9 months, and at end line to provide implementation data on the reach of the intervention. The assessments will use a rapid ethnographic assessment (REA) methodology, a structured approach that combines a variety of qualitative methods in a sequential format, designed to move from broad contextual understanding to a more specific focus on the study topic. This approach allows for the collection of focused data that addresses both the whole community context as a whole and the specific behaviours and HIV-prevention choices of mobile men.

The REA methodology comprises a set of structured activities such as community entry, spiral walks, observations, individual conversations/interviews, natural group discussions, and focus-group discussions. This is aimed at gathering a comprehensive perspective on the area of study and the communities living there. The rapid ethnographic assessment approach is conducted within a defined 15-day period [51]. Community entry is conducted a few months prior to the commencement of data collection. The research teams engage with the Community Advisory Boards (CABs) overseeing the chosen research sites for guidance on appropriate community entry specific to the sites concerned [52, 53]. This is followed by seeking the relevant permissions from the local leadership, including traditional, political, or community leaders, depending on the area [54]. The data collection methodology is standardised across study areas, ensuring consistency and rigour in the process [39, 55].

#### In-depth qualitative interviews with service users

One-on-one interviews will be conducted with up to 10% of participants across the sites, based on the visit schedule. These participants will be purposively selected to represent the emerging patterns of risk and adherence behaviours identified from the quantitative data. These interviews will provide insights into the experience, motivations, and barriers that facilitate or obstruct adoption of each PrEP modality during the randomised phase and the rationale for adoption of each modality during the choice phase. In addition to exploring individual behaviour changes, the interviews will capture changes in the communities/places the participants stay to inform the trial about context-specific factors which may affect trial outcomes (e.g. loss of employment options in a location and changes in health care provision) and how participants move between PrEP choices.

#### Exit interviews (choices and trial participation)

Exit interviews will be conducted with all participants as they exit the trial to capture their experiences and reflections on the study. These interviews will focus on their reasons for trial participation, their PrEP choices, and their overall experiences with the intervention. Participants who seroconvert at any time during follow-up will also be invited to take part in an in-depth interview as described above. These interviews will explore key factors contributing to seroconversion, including details about condomless sex or PrEP adherence since their last negative result, as well as the number and characteristics of new sexual partners during the follow-up period.

#### Group discussions

These will be conducted with a subset of participants, typically comprising approximately eight participants per group. Group discussions will be led by staff trained in qualitative research methods, who are independent of the clinic team, to ensure objectivity and minimise potential biases. Participants will be purposefully selected based on specific criteria, while others will be invited on an ad hoc basis to ensure diverse perspectives. These group discussions will aim to explore participants’ experiences, perceptions, and insights on the trial, including their motivations, challenges, and changes in behavior related to PrEP use.

#### Interviews with service providers

Structured debriefs and one-on-one interviews with community and counselling staff will be conducted by a social scientist during the study. Typically, these interviews will capture conversations observed or initiated by staff with and between participants, nonparticipants, clinic staff, and community workers. The notes will be anonymous and documented using a standardised template. Special attention will be given to understanding how participants transition between ED and daily PrEP through conversations with a range of service providers, including mobilisers/recruiters. To support reflection and inform ongoing training and supervision, peer navigators and clinical staff will be trained to keep very brief notes of their daily activities. These notes will be used during debriefing sessions to discuss key observations and challenges. These interviews will take place once recruitment is closed; additionally, endline interviews are scheduled with service providers, stakeholders, and community members. Peer navigators will be interviewed, and natural group discussions will be facilitated with various stakeholder groups, such as community leaders, Community Advisory Board members, and local healthcare providers, to gather perspectives on the study's implementation and impact.

#### Collaborative problem-solving meetings

Meetings will be held with healthcare workers from all sites to allow for collaborative problem-solving. Implementation of the study will be discussed, and modifications made for improvement will be documented to inform the implementation analysis (implementation and adoption domains of the RE-AIM framework).

#### Quantitative survey

The survey will collect data on demographics (age, relationship status, education, income, location), mobility patterns, mental health, and social economic factors [food security, social cohesion (network of friends), and support systems]. Surveys at months 9 and 18 will additionally explore participants’ PrEP choices and the ratings of their experiences with PrEP using a Likert scale.

#### Health economics

Cost data will be collected using bottom-up and top-down costing, drawing on expenditure reports, resource use from CRFs, from the provider perspective. We will combine these with relevant, up-to-date information on public sector prices and salaries in either country. At the mid-point of implementation, data collectors will conduct a time-and-motion study with study staff involved in implementation at each site to estimate staff time and resources used on key activities. Trial resource use will be adapted to represent potential rollout in routine care.

### Plans to promote participant retention and complete follow-up {18b}

Measures to support PrEP persistence will include pre-dose counselling at each visit and standard retention efforts if the participant fails to report for a subsequent visit. All participants with a missed visit will be followed up in the following way:At day 7 post a missed visit, the participant will be called using the telephone number provided at the most recent visit. After three unsuccessful attempts on subsequent days, at different times, the study team will carry out a home visit.Participants will be strongly encouraged to come in irrespective of whether or not they need PrEP.For CAB-LA participants who fail to return within 7 days, a home visit will be conducted (if permission has been given and it is safe to do so). Once contacted, a study visit will be rescheduled as soon as possible. However, due to the risk associated with stopping CAB-LA without coverage for the tail period, participants in the CAB-LA arm will be followed up with further phone calls and a home visit (if permitted) following the 7-day period. If the participant indicates that they wish to withdraw from the study, then the withdrawal will be documented, with the reason for withdrawal noted if provided. If the participant is in the CAB-LA arm, the participant will be encouraged to take oral PrEP to cover the tail period and will receive counselling on safe sex.

Participants will not be considered lost to follow-up until the trial has ended, unless they have left the country with no plans to return and with no means to ascertain HIV status. The date of loss to follow-up will be the date of their last study visit.

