## Trial design {8}

The Mobile Men study is a phase 3b, open-label, hybrid effectiveness-implementation type 2 trial to evaluate the initial implementation (scale-up) phase of CAB-LA as a PrEP option in men who are mobile for work in South Africa and Uganda with a high burden of HIV. The trial is a phase 3b, open-label, hybrid type 2 study with co-primary aims of effective use and implementation. The implementation of PrEP choice in mobile men is further investigated using a mixture of social science and health economics methods to understand reach, adoption, implementation, and maintenance. These include repeat rapid ethnographic assessments [39], qualitative interviews with users and providers, process evaluation, modelling and cost-effectiveness analysis.

A schematic representation of the trial design is shown in Fig. 1. Participants will be screened for HIV at enrolment. Those testing negative will be randomised to receive either oral or injectable PrEP for an initial 9-month period. Then, throughout the 9- to 18-month period following randomisation, participants will be offered a choice of oral or injectable PrEP. Participants determined as living with HIV at screening will be linked to care and followed up as a separate cohort alongside randomised trial participants.

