### Intervention description {11a}

Eligible participants (men testing HIV negative at screening) will be randomised in a 1:1 ratio to either Group A: oral TDF/FTC PrEP (ED or daily) or Group B: CAB-LA over 9 months. After 9 months, participants from both groups will be offered a choice of PrEP (oral TDF/FTC or CAB-LA) for a further 9 months, with the ability to change their choice as required.

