### Criteria for discontinuing or modifying allocated interventions {11b}

There are no planned modifications to oral TDF/FTC or CAB-LA PrEP dose. PrEP must be interrupted if a participant suffers a serious adverse event (SAE) that could be a drug reaction. Participants who have a positive hepatitis B virus test will be recalled if they are using CAB-LA PrEP and invited to switch to oral PrEP at the end of month 1 or counselled on alternative HIV prevention products.

If an individual chooses to stop PrEP, they may remain in the study, and the reason for stopping is documented.

The study investigator can also discontinue an individual from their allocated intervention for the following reasons:Confirmed HIV infectionUnacceptable toxicity that precludes the continuation of PrEPIntercurrent illness that prevents the safe use of PrEPEarly termination of study

Participants who enrol on the study and/or have received at least one CAB-LA injection or one PrEP tablet will be asked to remain in follow-up. However, participants may withdraw their consent for further visits at any point during the trial. Data that are already collected from participants who stop follow-up early may still be analysed, provided they have given consent.

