### Provisions for posttrial care {30}

All participants exiting the trial will be signposted and linked to HIV prevention services that provide PrEP. It may be that locally available CAB-LA is not yet in place, and this will be discussed with participants wanting to access it.

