### Outcomes {12}

The trial will have two co-primary outcomes:

User effectiveness co-primary outcome: This will assess persistent use of PrEP during the randomised period and throughout the full follow-up period. Persistent use of PrEP during the randomised period will be defined as a binary outcome. Participants randomised to the CAB-LA arm who receive all injections as per schedule (initial injection at month 0, followed by injections at months 1, 3, 5, and 7, with an acceptable window of ±7 days for each injection) will be considered “persistent on PrEP”. Participants who do not receive all injections as scheduled will be classified as “non-persistent on PrEP”, regardless of the frequency or timing of self-reported condomless sex. Participants randomised to the oral PrEP arm will be considered “persistent on PrEP” if they attend scheduled 3-monthly visits, receive sufficient PrEP to maintain supply until the next visit, and have detectable TFV-DP levels in DBS.During the full follow-up period (18 months), persistence will be assessed as a multinomial outcome with the following categories: single modality, consistent use; multiple modalities, consistent use; single or multiple modalities, inconsistent use; and never started PrEP.Implementation co-primary outcome: This will compare the adoption (uptake when offered and choice preference of the different modalities). Uptake is defined as the proportion of participants who are offered and subsequently take PrEP (oral PrEP arm versus CAB-LA arm) during the 9-month randomised period. Choice preference will be measured as the proportion of participants who choose and use each modality (daily or ED oral PrEP or CAB-LA), captured at the start and the end of the subsequent 9-month choice period.

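### As printed, the advice on withdrawal to take oral PrEP through the CAB-LA tail depends on randomised arm, so it misses a Group A man who chose CAB-LA after month 9

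*Protocol article*

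**What the plan says.** The retention section {18b} of the protocol article has three layers of follow-up after a missed visit.

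- **Everyone.** A call at day 7, repeated attempts, then a home visit.
- **Men on CAB-LA.** "For CAB-LA participants who fail to return within 7 days, a home visit will be conducted", subject to permission and safety.
- **Extra tracing because of the tail.** "due to the risk associated with stopping CAB-LA without coverage for the tail period, participants in the CAB-LA arm will be followed up" with more calls and a home visit.

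For a man who says he wants to withdraw, the section adds: "If the participant is in the CAB-LA arm, the participant will be encouraged to take oral PrEP to cover the tail period". He also receives safe-sex counselling.

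The design does not keep product and arm together for the whole trial. Under Trial design {8}, "throughout the 9- to 18-month period following randomisation, participants will be offered a choice of oral or injectable PrEP". Under Intervention description {11a}, "participants from both groups will be offered a choice of PrEP (oral TDF/FTC or CAB-LA) for a further 9 months", and they may change their choice as needed.

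**The concern.** The reason that the section gives for its tail measures is pharmacological: stopping CAB-LA leaves a period that needs cover. That risk belongs to anyone who has been injected, whatever his allocation. For the first 9 months the two coincide, because only Group B is scheduled for CAB-LA. From month 9 they separate, and a condition based on arm no longer identifies the injected men.

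At stake is a piece of safety advice on leaving the study. Read literally, two men with an equally recent injection could be advised differently because of an allocation that stopped governing product at month 9. The background section {6a} explains why the tail deserves care: it links CAB-LA's tail to drug resistance and to possible cross-resistance with dolutegravir.

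**Working it through.** No figure in the article needs reproducing. The check compares wording, with some simple arithmetic on visit months.

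**1. What *arm* means.** Outcomes {12} speaks of participants randomised to the CAB-LA arm. The randomisation procedure {16c} assigns each man to a randomisation arm. The blinding section {17a} refers to the arm to which participants are allocated. All three mean allocation.

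**2. Whether the section stops at month 9.** It does not. Its closing paragraph carries the definition of loss to follow-up through to the end of the trial, so the choice phase is included.

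**3. Whether another section brings the missing man in.** The only other mention of the tail is the modelling background in {6a}. Two general provisions help him, but neither is tail advice:

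- Section {11b} says that participants who enrol and/or "have received at least one CAB-LA injection or one PrEP tablet will be asked to remain in follow-up". A man who withdraws has declined that.
- Section {30} says "All participants exiting the trial will be signposted and linked to HIV prevention services that provide PrEP". That is linkage to services, not encouragement to take oral PrEP through the tail.

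**4. Two cases.** The randomised-phase schedule in {12} is "initial injection at month 0, followed by injections at months 1, 3, 5, and 7". Assume that a choice-phase starter follows the same spacing. A Group A man who starts at M9 is then injected at M9, M10 (9+1), M12 (9+3), M14 (9+5) and M16 (9+7).

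| Man | Last injection | Withdraws | Months since injection | Advice as printed |
|---|---|---|---|---|
| Group A, chose CAB-LA at M9 | M12 | M13 | 13 − 12 = 1 | No |
| Group B, moved to oral PrEP at M9 | M7 | M10 | 10 − 7 = 3 | Yes |

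The man closer to his last injection is the one left out.

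**5. Which condition works.** Arm covers the second man and misses the first. Current product covers the first and misses the second. Receipt of a CAB-LA injection covers both.

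**6. How many men.** Group A is 400 × 1/2 = 200. With p the share choosing CAB-LA and q the share of those who withdraw, the number is 200 × p × q. The article gives neither rate. Assumed values of p from 25% to 75% and q from 5% to 20% give:

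- 200 × 0.25 × 0.05 = 2.5
- 200 × 0.50 × 0.10 = 10
- 200 × 0.75 × 0.20 = 30

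The twelve-fold spread comes entirely from the assumptions, so this is an illustration and not an estimate.

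**The case against.** The strongest reply is that this is loose drafting with a clear purpose. The stated reason concerns the product, the sentence just before it refers to CAB-LA participants, and the exploratory objectives in {7} use *arms* loosely when describing men infected while using PrEP. Staff reading the section for its purpose would probably advise any injected man. The article also condenses protocol version 3.0, which may word the rule by product and may handle stopping in the choice phase in full.

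Much of this stands. It limits the point to the printed wording and is why the fix may need to touch only the article. It does not remove the point. The article has not left a detail to a fuller document; it states a condition for a safety measure, and that condition conflicts with its own design. Wording by product was available: the hepatitis B rule in {11b} applies to men who are using CAB-LA.

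A second reply is that the man is still followed up. For tracing, that is right. He gets the calls and home visit due to everyone and, on a natural reading, the 7-day visit for CAB-LA participants. The arm-worded sentence would add at most some calls and perhaps a repeat visit. Pre-dose counselling at each visit is also listed, although its content is not described. A reader might infer that Group A men who choose CAB-LA go untraced; the section does not support that.

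**Conclusion.** The point holds for the sentence on withdrawal advice. Read literally, it omits a Group A man who chose CAB-LA and then leaves the study. The tracing sentence shares the wording fault but has little practical effect.

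The size is minor. Those affected are an unknown part of 200 men, and other safeguards partly cover them. The primary 9-month comparison, the sample size and every other analysis are unchanged.

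The conclusion rests on reading *arm* as randomised allocation, as the rest of the article uses it, and on the printed text alone. Two stronger readings go beyond the documents:

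- A reader might infer that sites are withholding the advice. Nothing in the article shows what sites do, and version 3.0 may already be correct.
- A reader might infer that the advice must also be given at any stop of CAB-LA and at month-18 exit. The quoted sentence concerns withdrawal from the study. Stopping PrEP while staying in is dealt with in {11b}, and exit in {30}. Adding the advice there may be sensible, but it would be a new requirement and not a correction of this sentence.

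**What to change.** In both sentences of {18b}, replace *in the CAB-LA arm* with *who has received a CAB-LA injection during the trial, whatever the randomised group or period*. If the protocol defines a tail length, the condition may be limited to men still within it. Do not use current product as the condition, because that would drop Group B men who recently moved to oral PrEP and are covered now.

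First check protocol version 3.0. If it already words the rule by product, correct the article only. If it carries the arm wording, the change goes to ethics committees and regulators under {25}, with re-consent only if consent documents change. The running cost is a little more counselling and oral PrEP, both already used in the trial.

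Time is short. Recruitment ran from 20 August to 8 November 2024, so at publication on 10 November 2025 every man was at least 12 months in and past the point where arm fixed his product. The first month-18 visits fall due about 20 February 2026 (20 August 2024 plus 18 months), 102 days after publication, and follow-up is expected to end by April 2026. A clarifying note to sites, if the approvals allow one, would be the quickest route.
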